## 5.3 Secondary Outcomes Definitions

### 5.3.1 Hospitalisation due to UTI

Hospitalisation due to UTI is defined as an admission to a hospital for the management and treatment of a UTI (see primary outcome definition). This occurs when the infection is severe enough to require inpatient care, either due to complications or the inability to manage symptoms adequately in an outpatient setting.

### 5.3.2 Bacteraemic UTI/ urosepsis

Bacteraemic UTI refers to a UTI associated with bacteraemia, meaning the presence of bacteria in the bloodstream that has originated from the urinary tract. The diagnosis of a bacteraemic UTI is confirmed by blood cultures showing a pathogen typically associated with UTI, alongside clinical symptoms of a UTI. Urine cultures may also provide supportive evidence. The bacteraemia must be determined to have originated from the urinary tract, based on clinical judgment and/or laboratory investigations.

### 5.3.3 Urethral stricture

Urethral damage leading to clinically significant strictures refers to the development of narrowing or scarring of the urethra that results in significant impairment of urine flow or catheterization and requires clinical intervention. Active screening for urethral strictures will not be performed. If a patient report symptoms, diagnostic tests (such as urethroscopy or urethrography) will be performed to confirm the presence of a urethral stricture.

### 5.3.4 Kidney/bladder stone formation

Kidney and bladder stone formation is defined as the formation of stones in the kidneys or bladder that occur during the study period and are detected through diagnostic imaging (or cystoscopy) based on symptoms reported by the patient. Active screening for kidney/bladder stones will not be performed.

### 5.3.5 Episode of macroscopic hematuria

An episode of macroscopic hematuria refers to any occurrence of visible blood in the urine during the study period. Each distinct occurrence (even if it recurs after a period of absence) will be counted as a separate episode.

### 5.3.6 Patient satisfaction

Patient Satisfaction in this study is defined as the patient's overall satisfaction with their treatment experience, specifically regarding the use of intermittent catheters. Patient satisfaction is measured using the following PROMs:

- 1) ISCQ (Intermittent Self-Catheterization Satisfaction Questionnaire):
  - Purpose: Measures satisfaction with the process of intermittent self-catheterization.
  - Scoring: The ISCQ consists of multiple items rated on a 5-point Likert scale (1 = Strongly Agree, 2 = Agree, 3 = Neutral, 4 = Disagree, 5 = Strongly Disagree), where higher scores indicate greater satisfaction. The total score is calculated by averaging or summing the individual item scores.
  - Interpretation: Higher scores reflect greater satisfaction with the catheterization process.

### 2) InCaSaQ (Intermittent Catheterization Satisfaction Questionnaire):

- Purpose: Evaluates overall satisfaction with intermittent catheterization, including impact on daily life, convenience, and emotional experience.
- Scoring: Items are rated on a 5-point Likert scale (1 = Very Satisfied, 2 = Somewhat Satisfied, 3 = Neutral, 4 = Somewhat Dissatisfied, 5 = Very Dissatisfied), with higher scores indicating lower satisfaction. The total score is calculated by averaging or summing individual item responses.
- Interpretation: Higher scores indicate lower satisfaction, while lower scores represent greater satisfaction with catheterization.

### Quality of life (QoL)

QoL in this study is defined as the overall well-being and daily functioning of patients, as assessed using the EQ-5D-5L and SF-Qualiveen questionnaire.

- The EQ-5D-5L is a widely used tool to measure health-related quality of life across five dimensions: mobility, self-care, usual activities, pain/discomfort, and anxiety/depression. Each dimension is rated on a 5-level scale, ranging from no problems to extreme problems. The composite results from these five dimensions are used to derive a summary index, as well as a visual analog scale (VAS), which reflects the patient's subjective health status on a scale from 0 (worst possible health) to 100 (best possible health).
- The SF-Qualiveen (short form Qualiveen)
  - Purpose: Assesses the health related QoL for urinary disorders in patients.
  - Scoring: Items 1,2,5,6,7,8 use the following response scale:
    - 0 = not at all
    - 1 = Slightly
    - 2 = Moderately
    - 3 = Quite a bit
    - 4 = Extremely

Items 3,4 use the following response scale

- 4 = Never
  - 3 = Rarely
  - 2 = From time to time
  - 1 = Often
  - 0 = Always
- Interpretation: A lower score indicates a greater QoL.

### 5.3.7 Cost-effectiveness

The cost-effectiveness analysis (CEA) of reusable catheters versus single-use catheters will evaluate the incremental costs and incremental health effects of using reusable catheters, with health effects expressed in quality-adjusted life-years (QALYs). This analysis will follow the Dutch health economic guidelines (4) and be conducted by the Institute for Medical Technology Assessment (iMTA) at Erasmus University, Rotterdam. As such the societal perspective will be adopted, meaning that all costs and effects will be included in the analysis, regardless to whom they accrue. The time horizon

# STATISTICAL ANALYSIS PLAN for COMPaRE-trial

of the cost-effectiveness study will be equal to the timeframe of the clinical trial. Uncertainty concerning the incremental cost-effectiveness ratios, QALYs and costs will be assessed using bootstrapping, and this uncertainty will be presented graphically with the CE-acceptability curve. Data on medical healthcare utilisation (ie, volumes) will be collected both through hospital records and by means of the iMTA Medical Consumption Questionnaire (5). Data on productivity losses will be collected by means of the iMTA Productivity Costs Questionnaire (6). We will use a willingness to pay (WTP) threshold of €20 000/QALY, based on the reference value for cost-effectiveness determined by the National Healthcare Institute of The Netherlands (4). A study on health-economic burden of urinary-catheter-associated infection in England used a similar WTP threshold of £20 000/QALY based on the National Institute for Health and Care Excellence guidelines (7,8). Cost-effectiveness analysis will be presented in separate manuscript.

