### 10.2 Secondary study parameters

Secondary outcome measurements are symptom specific and quality of life related questionnaires (PGI-I, SF-36, EQ-5D-5L), the amount of urethral damage/strictures, kidney/bladder stone formation and changes in urinary culture/urinary microbiome. The ease of use of the catheters and patients' satisfaction will be evaluated by the ISC-Q and the InCaSaQ.

**Cost-effectiveness:** For the purpose of assessing the cost-effectiveness of reusable catheters, data will be collected on medical healthcare utilization, productivity losses and quality of life of patients alongside the clinical trial. In this cost-effectiveness study, incremental costs and incremental effects of reusable catheters over single-use catheters will be assessed, with effects expressed in quality-adjusted life-years (QALYs). The cost-effectiveness study will adhere to the Dutch health economic guidelines. As such, the societal perspective will be adopted, meaning that all costs and effects will be included in the analyses, regardless to whom they accrue. The time horizon of the cost-effectiveness study will be equal to the timeframe of the clinical trial.

Uncertainty concerning the ICER, QALYs and costs will be assessed using bootstrapping, and this uncertainty will be presented graphically with the CE-acceptability curve.

Data on medical healthcare utilization (i.e. volumes) will be collected both through the hospital and by means of the iMTA Medical Consumption Questionnaire (iMCQ). The iMCQ is a generic, non-disease specific, questionnaire to be filled out by the patient, and assesses the use of a variety of medical services. Hospital records can be used to obtain information about consultations and admissions for symptomatic UTIs.

Costs of catheters will be derived from the hospital financial administration. For single-use catheters, this is equal to the purchase price of the catheters. For reusable catheters,

costs of e.g. cleaning also need to be taken into account. This will be based on the time it takes plus possibly material to prepare a reusable catheter to be used again. This information will be estimates based on e.g. observations and/or expert opinion.

The data collected on healthcare utilization will be multiplied by standard unit cost prices, which are described in the Dutch costing manual.

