Data on productivity losses will be collected by means of the iMTA Productivity Costs Questionnaire (iPCQ). The iPCQ is a generic, non-disease specific, questionnaire. The iPCQ assesses productivity losses from absence from work or reduced efficiency at work and unpaid work. The data collected from the iPCQ will be monetized with hourly productivity costs derived from the Dutch costing manual. The five level version of the Euroqol 5D (EQ-5D-5L) will be used to measure quality of life of patients. The questionnaire consists of five dimensions, each with five answer levels. For cost-effectiveness studies, quality of life is often expressed in utilities, which present quality of life on a scale from 0 (death) to 1 (perfect health). The EQ-5D-5L can be used to calculate utilities using a Dutch tariff. QALYs are calculated by combining quality of life and survival. The EQ-5D-5L questionnaire will be administered at time 0, 6, 26 weeks and 52 weeks, whilst the iMCQ and iPCQ will be administered at time 6, 26 weeks and 52 weeks.

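### No adjustment of QALYs for week-0 EQ-5D-5L utility is specified in the cost-effectiveness analysis; adding it would gain precision at little cost

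*Combined protocol and SAP*

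**What the plan says.** Protocol section 10.2 and SAP section 5.3.7 describe the cost-effectiveness analysis in similar terms: incremental costs and incremental QALYs, a societal perspective, a horizon equal to the trial, and an acceptability curve. The only inferential method named is the bootstrap. The protocol says "Uncertainty concerning the ICER, QALYs and costs will be assessed using bootstrapping" and the SAP says "Uncertainty concerning the incremental cost-effectiveness ratios, QALYs and costs will be assessed using bootstrapping". The SAP adds a threshold: "We will use a willingness to pay (WTP) threshold of €20 000/QALY".

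On how the QALY is built, the protocol says only that "QALYs are calculated by combining quality of life and survival". On timing it says "The EQ-5D-5L questionnaire will be administered at time 0, 6, 26 weeks and 52 weeks". The cost questionnaires (iMCQ and iPCQ) start at week 6.

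No estimator, regression model or covariate is named for the QALY comparison, and SAP section 6 has no methods subsection for this analysis. The SAP's one statement on adjustment is in section 6.2.1. It covers the questionnaire mixed models and calls confounder adjustment unnecessary because randomisation is stratified. The stratification factors (Protocol 8.2, SAP 3.2) are centre, neurogenic or non-neurogenic cause, age, gender and menopausal status. Utility is not among them.

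**The concern.** A patient's utility at week 0 is likely to predict utility over the following year. If the arms differ by chance at week 0, part of that difference carries into the 12-month QALY difference and is read as an effect of the catheter. The reason given in SAP 6.2.1 for not adjusting does not help here, because stratification does not balance a variable that is not stratified on.

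The trial hopes to show that the catheters are similar on health, so a small true QALY difference is plausible. An ICER with a small denominator is unstable in size and sign. The bootstrap displays the noise from baseline imbalance but does not remove it. Cost-effectiveness is a stated secondary objective and cost saving is part of the rationale, so the precision of the increment matters.

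**Working it through.** The documents give no figure for the precision of the QALY comparison, so there is none to reproduce.

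**Inputs from the documents.** EQ-5D-5L at weeks 0, 6, 26 and 52 (Protocol 10.2); 154 effective cases per arm (SAP 6.3, used here only as a scale); EUR 20,000 per QALY (SAP 5.3.7).

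**Assumptions.** Trapezoidal area under the utility curve; complete data; utility SD 0.20-0.25; equal correlation r between any two visits, 0.3-0.7.

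**Weights.** Half the adjoining intervals divided by 52: week 0 = 3/52 = 0.058; week 6 = 13/52 = 0.250; week 26 = 23/52 = 0.442; week 52 = 13/52 = 0.250. Sum of squared weights = (9 + 169 + 529 + 169)/2704 = 0.324.

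**Formulas.**
- Slope of QALY on week-0 utility: b = 0.058 + 0.942r
- QALY variance in units of SD²: v = 0.324 + 0.676r
- Share of QALY variance removed by adjustment: b²/v
- Standard error of the baseline difference: SD × √(2/154) = 0.0228 (SD 0.20) to 0.0285 (SD 0.25)
- Shift in incremental QALY for a one-standard-error imbalance: b × that standard error

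| r | b | v | variance cut | CI narrower by | shift, SD 0.20 to 0.25 | × EUR 20,000 |
|---|---|---|---|---|---|---|
| 0.3 | 0.340 | 0.527 | 22% | 12% | 0.0078 to 0.0097 | EUR 155-194 |
| 0.5 | 0.529 | 0.662 | 42% | 24% | 0.0121 to 0.0151 | EUR 241-301 |
| 0.7 | 0.717 | 0.797 | 65% | 40% | 0.0163 to 0.0204 | EUR 327-409 |

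The interval narrows by 1 − √(1 − variance cut). The direct week-0 weight alone gives a shift of only 0.0013-0.0016 QALY, so most of the effect comes through correlation with later scores.

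**Sensitivity.** With 152 per arm, SD 0.20-0.30 and r 0.4-0.8, the one-standard-error shift is 0.010-0.028 QALY and the interval narrows by 17-51%. If correlation instead falls linearly from 0.85 at short lags to 0.4-0.8 at 52 weeks, the interval narrows by 33-54%. That structure has high early correlations; weak correlation of week 0 with weeks 26 and 52 would give less. In 5,000 simulated trials (SD 0.25, r = 0.6, 152 per arm, no true difference) the estimate had SD 0.0245 unadjusted and 0.0169 adjusted, both centred on zero.

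**Scale against costs.** Protocol section 1 gives potential savings of EUR 13,184,437.50 at EUR 1.03 per catheter and EUR 23,272,125.00 at EUR 1.70. If both use the same volume, that is 10,087,687.50 / 0.67 = 15,056,250 catheters. At the 1,825 per patient-year in SAP 2.1 this is 8,250 patients, so the implied saving is EUR 1,598-2,821 per patient-year. The shift of EUR 155-409 is about 5-26% of that. Cancelling the saving at EUR 20,000 per QALY needs a loss of 0.080-0.141 QALY. The unadjusted standard error, SD × √(2v/154), runs from 0.0165 to 0.0254, so this is at least 0.0799/0.0254 = 3.1 standard errors. SAP 2.1 also says four catheters a day, which is 1,460 a year; on that count there are 10,312.5 patients, the saving is EUR 1,278-2,257, and the figure is 0.0639/0.0254 = 2.5 standard errors.

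**The case against.** The strongest objection is that the plan does not say what a reader might infer, namely that QALYs will be compared unadjusted. It names no estimator, and a bootstrap is equally compatible with a regression-adjusted increment. This stands: the documents support only the statement that no adjustment is specified. The area-under-the-curve rule is also an assumption. The analysis is assigned to a specialist institute and deferred to Dutch guidelines that may address baseline utility. That cannot be checked here, so it neither settles the point nor excuses leaving the method open until data are seen.

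A reader might also infer bias, with imbalance passing in full into the ICER. It does not. The unadjusted difference is unbiased over randomisations, the bootstrap interval already reflects chance imbalance, and the slope is 0.34-0.72 rather than 1. The matter is efficiency and a shift in the one realised trial.

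Nor do the documents support the inference that the decision at EUR 20,000 per QALY is at risk. The implied supply saving is several times the shift. That saving is rough: it appears to cover catheter supply only, and cleaning time, healthcare use, productivity and the single-use catheters permitted in the intervention arm would change it.

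Finally, the gain in QALY variance overstates the gain in net benefit, because costs have no baseline measure. This also stands. The SAP says "Cost-effectiveness analysis will be presented in separate manuscript", so the primary report does not depend on this analysis.

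**Conclusion.** The point holds as a cheap improvement to a secondary analysis. Incremental QALYs with bootstrapped uncertainty are planned, week-0 utility is collected, it is not a stratification factor, and no adjustment for it is specified. Under the stated assumptions (trapezoidal QALY, SD 0.20-0.25, equal correlation 0.3-0.7, 154 per arm, complete data), a one-standard-error imbalance moves the increment by 0.008-0.020 QALY, and adjustment removes 22-65% of the QALY variance. The size depends mainly on the correlation of week 0 with later visits, which the documents do not give. The proportional gain for net benefit will be smaller. No bias and no change of decision has been shown, and the primary non-inferiority test is untouched.

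**What to change.** In SAP 5.3.7 and Protocol 10.2:

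1. State the QALY formula, including the visit weights or interpolation rule.
2. Estimate the incremental QALY by regressing each patient's QALY on arm and week-0 EQ-5D-5L utility, refitted within each bootstrap replicate.
3. Use that increment for the ICER and the acceptability curve.
4. Report the unadjusted increment as a sensitivity analysis.
5. Give a rule for a missing week-0 questionnaire, for example mean imputation of the baseline covariate. If the QALY itself uses the week-0 value, say how it is formed for those patients.

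No new data are needed. The cost is one covariate in the bootstrap code, plus the missing-baseline rule, which is the only real downside. Costs cannot be adjusted for their own baseline, because the cost questionnaires start at week 6.

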## 5.3.8 Patient opinion

Patient opinion regarding healthcare costs and environmental burden in the context of CISC refers to patients' perceptions and attitudes towards the financial and environmental impacts of using single-use versus reusable catheters. This outcome is assessed using two statement-based questions, each rated on a Likert scale from 1 to 5 (where 1 = fully agree, 5 = fully disagree).

## 5.3.9 Changes in urine cultures over time

Changes in urine cultures over time refers to the evaluation of the bacterial composition of urine samples collected at week 0 (baseline) and week 52 (final visit). This outcome will focus on identifying any changes in bacterial species present in the urine.

### Overview of Outcomes

| Level     | Outcome                        | Timeframe    | Type        |
|-----------|--------------------------------|--------------|-------------|
| Primary   | UTIs per month                 | During trial | Continuous  |
| Secondary | UTI during follow-up           | During trial | Dichotomous |
|           | Hospitalisation due to UTI     | During trial | Dichotomous |
|           | Bacteraemic UTI/ urosepsis     | During trial | Dichotomous |
|           | Urethral stricture             | During trial | Dichotomous |
|           | Bladder/kidney stone formation | During trial | Dichotomous |
|           | Epididymo-orchitis             | During trial | Dichotomous |
|           | Prostatitis                    | During trial | Dichotomous |

## STATISTICAL ANALYSIS PLAN for COMPaRE-trial

---

|                                     |                                          |                                        |
|-------------------------------------|------------------------------------------|----------------------------------------|
| Episodes of macroscopic hematuria   | During trial                             | Dichotomous                            |
| Hospitalisation, not study linked   | During trial                             | Dichotomous                            |
| Urethral irritation                 | During trial                             | Dichotomous                            |
| Pyelonefritis                       | During trial                             | Dichotomous                            |
| ISCQ-score (patient satisfaction)   | During trial (4 time points)             | Continuous                             |
| InCaSa-score (patient satisfaction) | During trial (4 time points)             | Continuous                             |
| SF-Qualiveen                        | During trial (4 time points)             | Continuous                             |
| Index and EQ VAS-score (QoL)        | During trial (4 time points)             | Continuous                             |
| QALYs and total costs               | During trial                             | Continuous                             |
| Patient opinion (Likert scale)      | Baseline and final visit                 | Categorical                            |
| Changes in urine cultures (S)AE     | Baseline and final visit
During trial | Dichotomous
Categorical/dichotomous |

---

---

## 6 Analysis Methods

### 6.1 Methods for Primary Outcome

#### 6.1.1 Descriptive Statistics

All categorical (binary and ordinal) data will be summarised using frequency counts and percentages of patient incidence. Percentages will be calculated using the study population (FAS); any exceptions to this will be highlighted in the table footnote. The continuous variables will be summarised using number of patients (N), mean, standard deviation (SD), median, 25/75 percentile and range

# STATISTICAL ANALYSIS PLAN for COMPaRE-trial

---

(minimum/maximum). In general, minimum and maximum will be presented to the same degree of precision as data is recorded, with mean and median having 1 additional place after the decimal and standard deviation having 1 additional places after the decimal. Percentages less than 100 will be displayed to 1 place after the decimal, where space permits.

## 6.1.2 Primary Analysis

For the primary outcome, the incidence rate in each group is the total number of UTIs divided by the total follow-up time, reported with 95% confidence intervals calculated using bootstrap procedure. The absolute difference between groups will be calculated and reported with a 95% bootstrap confidence interval. Non-inferiority will be concluded if the upper limit of the CI is below the non-inferiority margin of 7%. The incidence rate ratio (IRR) with a 95% CI will be estimated in both arms using a poisson or negative binomial regression model (in case there is overdispersion of the data). All analyses will be conducted using R version 4.2.1 (R Foundation for Statistical Analysis, Vienna, Austria).

## 6.1.3 Missing Data

For the primary analysis missing data will not be imputed.

## 6.1.4 Methods (S)AE Primary Outcomes

### 6.1.4.1 Descriptive Statistics

The frequency (n) and percentage (%) of subjects with any (s)AEs will be summarised by treatment group. SAEs will be detailed and presented in a separate table.

### 6.1.4.2 Missing Data

Missing data on (S)AE will not be imputed.

## 6.2 Methods for secondary outcomes

### 6.2.1 Methods for outcomes of questionnaires (ISCQ, InCaSaQ, EQ-5D-5L, SF-Qualiveen, PGI-I).

#### 6.2.1.1 Descriptive Statistics

Continuous variables will be described using means and standard deviations. Categorical variables will be described using frequency (n) and percentages (%).

Linear mixed models (LMMs) will be used to assess longitudinal trajectories of the PROs between the two treatment arms. The models will include fixed effects for treatment group, time, and the interaction between time and treatment group. Since all questionnaires are collected at the same follow-up scheme, time will be used as a categorical variable (9). To account for within-subject correlation, a random intercept will be included for each patient. Adjustment for confounders is deemed unnecessary, as stratified randomization is applied. Baseline, as well as the scores at 6 weeks, 26 weeks and 52 weeks are included in the model. Longitudinal linear mixed model analyses correct for missing responses at random (9). The interaction between “time x treatment arm” is included in the model as interaction to assess whether the treatment arm had different effects on the outcomes of the questionnaires at different points in time (9).

A post hoc subgroup analysis is conducted to examine outcomes by gender (male vs. female), age

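### The questionnaire models use a random intercept alone and leave the baseline arm means free, which loses precision and can misstate the change-from-baseline standard errors

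*Combined protocol and SAP*

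**What the plan says.** SAP 6.2.1.1 covers ISCQ, InCaSaQ, EQ-5D-5L, SF-Qualiveen and PGI-I.

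- **Fixed effects:** "The models will include fixed effects for treatment group, time, and the interaction between time and treatment group". Time is categorical.
- **Covariance:** "a random intercept will be included for each patient". Neither 6.2.1.1 nor 6.2.1.2 names a residual structure, a random slope or a robust standard error.
- **Baseline:** "Baseline, as well as the scores at 6 weeks, 26 weeks and 52 weeks are included in the model". With an arm main effect and categorical time, the week-0 score is one of the outcomes, and the arm means at week 0 are estimated freely.
- **Covariates:** "Adjustment for confounders is deemed unnecessary, as stratified randomization is applied".
- **Target:** the arm-by-time interaction, to see whether the arm effect differs between visits. No single-visit contrast is named.

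The visit times agree with protocol 10.2: "The EQ-5D-5L questionnaire will be administered at time 0, 6, 26 weeks and 52 weeks". The SAP overview of outcomes lists ISCQ, InCaSaQ, SF-Qualiveen and EQ-5D-5L at four time points and gives no visit priority. In the protocol's schedule (section 3), PGI-I first appears at week 6, and protocol 8.1.2 describes it as for the intervention group.

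**The concern.** There are two separate issues.

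**Precision.** Because the baseline arm means are free, each arm-by-time coefficient is a difference between arms in change from baseline. In a randomised trial the arms share a baseline mean by design, and an analysis that uses this fact is more precise. The SAP's reason for not adjusting does not cover baseline scores. The stratification factors in SAP 3.2 are centre, cause of catheterisation, age, gender and menopausal status, and no questionnaire score is among them.

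**Calibration.** A random intercept alone imposes one variance and one correlation on all pairs of visits, whether 6 or 52 weeks apart. If scores far apart in time are less alike than scores close together, the model averages over the pairs. It then understates the variance of the longest change and overstates that of the shortest.

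At stake are the intervals and two-sided 5% tests for satisfaction and quality of life, on which SAP 2.3.2 bases the objective that reusable catheters are not less efficient.

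**Working it through.** The documents give no SD, between-visit correlation or precision for any questionnaire, so there is no figure of the plan to reproduce. All correlations below are assumptions. N is 193 per arm (SAP 6.3), the SD is set to 1, and data are complete unless stated.

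**Formulas.** Let r be the correlation between week 0 and the visit in question, and r̄ the mean of the six pairwise correlations.

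- Change contrast (arm-by-time coefficient): true SE = √[(2/n)·2(1−r)]; random-intercept model SE = √[(2/n)·2(1−r̄)]. Their ratio is √[(1−r̄)/(1−r)].
- Arm difference at week 52: true SE = √(2/n). The model uses the average variance over visits, so with equal variances the two agree.
- Baseline-adjusted difference: SE = √[(2/n)(1−r²)].

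**Precision.** The adjusted variance divided by the change variance is (1−r²)/[2(1−r)] = (1+r)/2, a saving of (1−r)/2. Against the week-52 difference the saving is r².

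- r = 0.60: (1−0.60)/2 = 20%; 0.60² = 36%. SEs: change 0.091, difference 0.102, adjusted 0.081.
- r = 0.45: 28% and 20%. SEs: 0.107, 0.102, 0.091.
- r = 0.34: 33% and 11%. SEs: 0.117, 0.102, 0.096.

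**Calibration of the change contrast.** Assume correlation a·exp(−gap/τ), with the gap in weeks.

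| a, τ | r, weeks 0–6 | r, weeks 0–52 | r̄ | SE ratio, week 52 | 95% CI coverage, week 52 | SE ratio, week 6 |
|---|---|---|---|---|---|---|
| constant 0.60 | 0.60 | 0.60 | 0.60 | 1.00 | 95.0% | 1.00 |
| 0.75, 150 | 0.72 | 0.53 | 0.62 | 0.90 | 92.2% | 1.17 |
| 0.80, 90 | 0.75 | 0.45 | 0.59 | 0.87 | 91.1% | 1.28 |
| 0.80, 60 | 0.72 | 0.34 | 0.51 | 0.86 | 90.9% | 1.34 |
| 0.70, 40 | 0.60 | 0.19 | 0.36 | 0.89 | 91.8% | 1.27 |

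For the third row the week-52 ratio is √[(1−0.586)/(1−0.449)] = 0.867, and coverage is 2Φ(1.96 × 0.867) − 1 = 91.1%.

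Two other assumed sets of correlations with baseline (weeks 6, 26, 52) widen the range:

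- 0.80, 0.65, 0.50 with r̄ = 0.658: √(0.342/0.50) = 0.827, true size of a 5% test 10.5%.
- 0.74, 0.61, 0.54: ratio 0.916, size 7.3%.

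This gives the 8–17%.

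**Simulation.** Random-intercept REML was run 3,000 times for each of the first three decay rows. Coverage of the week-52 change contrast was 91.3–92.6% with complete data and 90.3–92.6% with about 20% dropout at random.

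**Week-52 arm difference, same three patterns.** Coverage was 95.0% in closed form, 94.6–94.9% simulated with complete data, and 93.8–94.2% with 20% dropout. Unequal variances move it either way: 91.8% if the SD rises from 1.0 to 1.3 over the visits, 97.6% if it falls from 1.3 to 1.0.

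**Joint 3-df interaction test.** Under the four decay rows its true size is about 5.4–5.9%. The week-6 and week-52 errors largely offset each other.

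**The case against.** A reader might infer that the week-52 interval is simply too narrow. The documents do not support that. It needs a decaying correlation, on which they are silent, and it needs the reported result to be the week-52 interaction coefficient, which the SAP does not specify. If the plain arm difference at week 52 is reported, the interval is close to nominal with equal variances and can be too wide if the SD falls. If the interaction is tested jointly, as the aim of comparing trajectories suggests, the distortion is small.

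It is also tempting to treat week 52 as the main visit for these scales. The protocol schedule labels it as the endpoint, but that is the end-of-follow-up visit, and the SAP overview ranks none of the four time points above the others. Nor does the plan ignore baseline. It is in the model, and a difference in change is a valid, unbiased comparison in a randomised trial, so baseline handling is a matter of efficiency.

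Finally, these are secondary outcomes with no stated margin. All of this stands, and it limits how much the point matters. It does not remove the precision loss, which needs no assumption about decay, or the lack of any safeguard against a misspecified covariance.

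**Conclusion.** The point holds as a cheap improvement limited to secondary outcomes. The primary analysis and the non-inferiority rule (SAP 3.3.3 and 6.1.2) are untouched.

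The loss of precision holds on either reading of the reported contrast, for any r strictly between 0 and 1. Only its size depends on the assumed r. The understated standard error is conditional: it applies to the week-52 arm-by-time coefficient when correlation falls with time, with the week-6 coefficient erring the other way. It vanishes under constant correlation and equal variances.

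The four-visit description does not fit PGI-I, which has no week-0 entry in the protocol schedule. The general timing sentence in protocol 8.1.2 mentions baseline for the group of scales that includes it, so the two places should be reconciled.

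**What to change.** In SAP 6.2.1.1, for ISCQ, InCaSaQ, EQ-5D-5L and SF-Qualiveen:

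1. Replace the random intercept with an unstructured covariance over the four visits. This has 10 parameters (4 variances and 6 covariances) for 386 patients. State in advance what is used if the model does not converge, such as heterogeneous Toeplitz or robust standard errors.
2. Either constrain the arms to a common mean at week 0, or move the baseline score to a covariate crossed with time and keep weeks 6, 26 and 52 as outcomes.
3. Name the reported contrasts: the arm difference with 95% CI at weeks 6, 26 and 52.
4. Give PGI-I a separate paragraph that says which arm or arms complete it and how scores without a baseline are summarised.

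The cost is a few sentences in the SAP and a few lines of code. The downside is a slightly more complex model and the need for the convergence fallback.
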